**Methods:**

Eighty patients with LD-SCLC after response to chest chemoradiotherapy will be enrolled. Patients will be followed up by brain MRI every 3 to 6 months up to 3 years. Neurocognitive function tests will be performed at baseline and after 12 and 24 months. Patients who develop brain metastases will be irradiated with stereotactic (SRT) or whole brain RT (WBRT). The primary endpoint is overall survival. The secondary endpoints are: response rate to radiotherapy of early detected brain metastases, analysis of efficacy of SRT and WBRT; assessment and analysis of neurocognitive functions and QoL in the studied cohorts: QLQ-C30 questionnaire and the California Verbal Learning Test, Color connection test, Benton visual retention test, and verbal fluency test will be carried out.

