**Discussion:**

The results of this trial may contribute to changing of LD-SCLC clinical management by deescalating the treatment. There is a lack of prospective, recent studies in LD-SCLC patients with omission of PCI and modern radiation therapy technologies for developed brain metastases. The comprehensive neurocognitive function testing will help to assess the impact of modern radiotherapy (SRT) compared with WBRT and no-PCI in SCLC patients. A subgroup of long-term survivors, who will not develop brain metastases, will not be exposed to unnecessary brain irradiation with its deleterious consequences. The limitation of our study is a lack of parallel randomized control arm. This is a potential source of bias; however, randomized study will be difficult to complete for two major reasons: (1) limited population of LD-SCLC eligible for the study and (2) opinions of our patients, who after information and discussion about benefits and potential harms of PCI, often choose to omit PCI in our practice.

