### Statistical assumptions

The sample size of the studied group of patients was calculated using the online SWOG data calculator (Southwest Oncology Group). Based on the published data (in 2013) from our cancer center reporting the survival of patients with SCLC treated in our institution in 2003 to 2006, the expected number of patients was calculated. The 2-year survival was 36% for a group of 138 LD-SCLC treated in our institution [17]. We assumed that the 2-year survival in the studied group will be at least 50%. Taking α < 0.1 and a power of 0.80, the required sample size is 80 patients. Patients with diagnosed LD-SCLC, after radical treatment with remission or at least a good response after radical therapy, will be eligible for the study. Patients would have had radical radiotherapy to the chest with chemotherapy according to current international guidelines and institutional protocols. A detailed medical history will be collected regarding SCLC and comorbidities. During the qualification visit, the remission or good response should be confirmed based on chest/abdomen/pelvis CT examinations. After obtaining the patient’s informed consent to participate in the clinical trial, a brain MRI (MRI-1) will be performed and a baseline assessment of cognitive functions will be carried out using the battery of test listed below. Patients who at MRI-1 will be diagnosed with cerebral metastasis, depending on the size and number of lesions, will be eligible for WBRT (whole brain irradiation) or SRT (brain stereotactic radiotherapy). We propose SRT eligibility treatment criteria as in NSCLC according to the standards of the participating centers. All participating radiotherapy centers must have experience in SRT of brain metastases and up-to-date radiotherapy equipment suitable for SRT. Subjects who will not have cerebral metastases in the MRI-1 after chemoradiotherapy will have their next follow-up every 3 months (± 2 weeks) up to 2 years, and then every 6 months (± 2 weeks) up to 3 years. At the qualifying visit before MRI-1, and then every 6 months ±2 weeks), the patients will have a cognitive examination performed using dedicated neuropsychological tests and QoL assessment using the QLQ-C30 questionnaire. The tests will be conducted in the following order: California verbal learning test (CVLT) with a delay of 15 min, Color connection test (CCT), CVLT (after delay), Benton visual retention test (BNRT), verbal fluency test (VFT) by the certified psychologist (Table 2).

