
**Table 2 Tab2:** Schedule for observation of patients qualified for the study (24 months)

	initial visit	observation-months									
Months	−1	3	6	9	12	15	18	21	24	30	36
Patient consent	x										
Patient history and physical exam	x	x	x	x	x	x	x	x	x	x	x
Neurocognitive tests	x		x		x				x		
Quality of life	x				x				x		
Brain MRI scan and chest/abdomen CT scan	x	x	x	x	x	x	x	x	x	x	x

Overall survival will be measured using the Kaplan-Meier method from the date of the chest chemoradiotherapy start day until death, with preplanned subgroup analysis of brain metastases-free and brain metastases group. Assessment of clinical response by RECIST 1.1 criteria after brain SRT and WBRT in the brain will be determined. Comparison of neurocognitive tests scores in the subgroup with developed brain metastases before and after SRT and/or WBRT will be carried out using Student’s *t* test or in case of non-normal distribution by nonparametric tests. In the subgroup without developed brain metastases, the analysis of tests scores will be done in the same way. QoL scores and neurocognitive test scores will also be compared between subgroups with and without metastases to the brain with nonparametric tests. The tested differences will be considered significant if *p* value is less than 0.05. In order to consider important prognostic factors and stratification factors related to the disease and the treatment modality in the final analysis, initial tumor volume of intrathoracic disease (GTV), mode of chemoradiation treatment: concurrent vs sequential and bid (irradiation twice daily) vs oid (irradiation once daily) will be recorded in the data base.

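### The cognitive and quality-of-life comparisons carry a blanket p<0.05 rule with no exploratory status, so an isolated significant result would mean little

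*Protocol article*

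**What the plan says.** All references are to the protocol article. In Methods/design, Statistical assumptions, the text after Table 2 plans three sets of comparisons:

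1. Within patients who develop brain metastases: "Comparison of neurocognitive tests scores in the subgroup with developed brain metastases before and after SRT and/or WBRT will be carried out".
2. Within patients who do not: "In the subgroup without developed brain metastases, the analysis of tests scores will be done in the same way".
3. Between the two subgroups: "QoL scores and neurocognitive test scores will also be compared between subgroups with and without metastases to the brain with nonparametric tests".

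The rule that follows covers all of them: "The tested differences will be considered significant if *p* value is less than 0.05".

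The same section lists the battery: "California verbal learning test (CVLT) with a delay of 15 min, Color connection test (CCT), CVLT (after delay), Benton visual retention test (BNRT), verbal fluency". That is four instruments, or five scores if immediate and delayed CVLT recall are counted separately. Quality of life is measured by QLQ-C30.

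The number of visits is not settled. The abstract says "Neurocognitive function tests will be performed at baseline and after 12 and 24 months". Table 2 marks cognition at 6, 12 and 24 months and quality of life at 12 and 24. The Methods text has both assessed every six months.

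The Background lists cognition and quality of life as the third secondary goal. The Discussion part of the abstract says what the battery is for: "The comprehensive neurocognitive function testing will help to assess the impact of modern radiotherapy (SRT) compared with WBRT and no-PCI in SCLC patients".

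**The concern.** The article fixes a decision rule for a whole family of tests, and the rule works test by test. It names no score, time point or contrast as the one that answers the cognitive question, and it gives none of them exploratory status. Applied as written, it lets any one score at any visit in any of the three sets be reported as a significant difference. It also offers no way to settle the matter if two instruments or two visits disagree.

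Sparing cognition is a central part of the article's rationale for omitting PCI. An isolated significant score could therefore be read as evidence about SRT, WBRT or the omission of PCI, although chance alone would produce one fairly often.

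**Working it through.** **The plan's own figure.** The article gives 0.05 per test. It states no error rate for the family, so there is none to reproduce.

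**Inputs from the article.** Four cognitive instruments, counted as one score each; three sets of comparisons; threshold 0.05; post-baseline cognitive visits at 12 and 24 months (abstract) or 6, 12 and 24 months (Table 2).

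**Assumptions.** Tests are two-sided, since the article does not say. No true difference exists in any score. The subgroups have 32 patients with and 48 without metastases, which sum to the planned 80. Correlation between tests is 0.3 to 0.8, and between visits 0.5. The test statistics are treated as normal.

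**Step 1: count the tests.** Set 1 is tied to radiotherapy, so it is counted once whatever the number of visits. With T post-baseline visits, the cognitive count is 4 + 4T + 4T.

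- T = 1: 4 + 4 + 4 = 12
- T = 2: 4 + 8 + 8 = 20
- T = 3: 4 + 12 + 12 = 28

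QLQ-C30 is left out, so these counts are on the low side for each T.

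**Step 2: one contrast at one visit.** For four independent tests, 1 − 0.95^4 = 0.185. With equally correlated statistics the chance is 0.156 at correlation 0.5 and 0.114 at 0.8. Even here it is about 2.3 to 3.7 times 0.05.

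**Step 3: ceiling under independence.** This is 1 − 0.95^k:

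- k = 12: 0.460
- k = 20: 0.642
- k = 28: 0.762

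**Step 4: correlated structure.** For each score and visit, mean changes were drawn for the two subgroups. The within-subgroup statistics and the difference between subgroups were formed from the same draws, so the dependence between the three sets is kept. With 200,000 draws, the chance of at least one |z| > 1.96 is:

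| Visits | Tests | Corr. 0.3 | Corr. 0.5 | Corr. 0.8 |
|---|---|---|---|---|
| 1 | 12 | 0.36 | 0.33 | 0.24 |
| 2 | 20 | 0.52 | 0.47 | 0.36 |
| 3 | 28 | 0.62 | 0.58 | 0.45 |

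**Step 5: a second layout.** This simulation used paired t tests within subgroups, Mann-Whitney tests between them, assumed groups of 30 and 50, and QLQ-C30 counted as one score. Correlations were 0.3 to 0.7 between scores and 0.5 to 0.7 over time. It gave 0.36 to 0.47 for one visit (4 + 4 + 5 = 13 tests) and 0.57 to 0.73 for three visits (4 + 12 + 15 = 31 tests, one more than Table 2 supports because QoL is not scheduled at 6 months). The size of the inflation does not depend on the normal approximation in step 4.

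**The case against.** The strongest reply is that a 0.05 threshold is a convention, and that a hierarchy, a key contrast or an exploratory label is commonly left to a statistical analysis plan that is not shown. That is right as far as it goes: the absence of a multiplicity section is no finding here. What remains is that the article itself states when a difference counts as significant. A later plan would have to override that sentence.

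Several stronger readings are tempting, and the documents do not support them.

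- *A false cognitive finding is likely.* With one time point the chance is 0.24 to 0.36, and for one contrast at one visit 0.11 to 0.19. It exceeds one half only with two or three visits and at the lower correlations. The text after Table 2 does not say how many visits will be tested.
- *Two visits mean at least 24 tests.* That would count the before/after radiotherapy comparison once per visit. The wording describes one comparison anchored to radiotherapy, which gives 20.
- *The abstract draws a treatment conclusion from the battery.* It states a purpose, and it acknowledges the lack of a control arm as a potential source of bias.
- *The trial's main conclusion is at risk.* Survival has its own alpha and sample size, and this rule touches neither.

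It can also be said that the subgroups are not randomised and are defined by an event that may occur after enrolment. A p-value could not carry a causal claim between them even with perfect error control. This stands, and it supports an exploratory label rather than a formal adjustment. Finally, these scores also serve to detect decline, so a remedy that made them conditional on one key test would be a poor trade.

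**Conclusion.** The point holds as a limited one about what the cognitive and quality-of-life results may be called. Under the stated rule, the chance of at least one falsely significant cognitive result is about 0.24 to 0.36 with one time point, 0.36 to 0.52 with two and 0.45 to 0.62 with the three cognitive visits of Table 2, where a reader would take 0.05 at face value. These figures rest on an inferred test count, assumed subgroup sizes and correlations, and no true difference in any score. Counting delayed CVLT recall, QLQ-C30 or its subscales as further scores would raise them. An unseen analysis plan may already deal with the matter. The consequence is confined to the secondary cognitive and quality-of-life conclusions. It is worth correcting because correction is cheap and changes what can be claimed.

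**What to change.** Replace the p<0.05 sentence with wording along these lines:

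*The cognitive and quality-of-life comparisons are secondary and exploratory. All scores and time points are reported as estimates with 95% confidence intervals and nominal, unadjusted p-values. No difference is called significant on the basis of an isolated p<0.05.*

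If the sponsor wants one confirmatory cognitive statement, it should name in advance one score, one time point and one of the three planned contrasts with its population, tested at two-sided 0.05. All other scores should still be reported in full, whatever that test shows.

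The cost is a few sentences, with no extra patients, visits or data. The downside is that an isolated nominal p<0.05 can no longer be presented as a significant finding.

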## Discussion

The trial design was discussed with several SCLC patients by SN. Patients diagnosed with SCLC in our current clinical practice after being informed about benefits and potential harms of PCI often consciously resign from PCI; therefore, prospective study without control arm with PCI was chosen instead of randomized controlled trial. Participation in the study is completely voluntary, the patient will be informed about the generally recognized standard of therapeutic treatment and the possible consequences of participating in the study. Regular patient controls will be carried out in the presence of experienced specialists, and when the disease progresses, the patient will be treated immediately in an optimal manner according to current clinical practice. Personal data of the subject will be closely guarded. Project documentation will be protected so that undesirable persons will not have access to it. At any time during the project, the patient has the right to resign from further participation.

There are 3 radiotherapy centers that have declared to take part in this study: (1) Szpital MSWiA z Warmińsko-Mazurskim Centrum Onkologii w Olsztynie, (2) Ośrodek Radioterapii i usprawniania NU-MED w Elblągu, (3) Klinika Onkologii i Radioterapii Gdańskiego Uniwersytetu Medycznego w Gdańsku. The planned enrollment time is 24 months. The first patient was enrolled in Szpital MSWiA z Warmińsko-Mazurskim Centrum Onkologii w Olsztynie in September 2019. In case of enrolment rate slower than expected, additional radiotherapy centers in Poland will be approached to participate in the study.

## Data Availability

The data sets used and/or analyzed during the current study are available from the corresponding author on reasonable request.

## Abbreviations

PCI: Prophylactic cranial irradiation
LD-SCLC: Limited disease small cell lung cancer
MRI: Magnetic resonance imaging
SRT: Stereotactic radiotherapy
WBRT: Whole brain radiotherapy
QoL: Quality of life
CNS: Central nervous system
CT: Computed tomography
HR: Hazard ratio
ED-SCLC: Extensive disease small cell lung cancer
RTOG: Radiation Therapy Oncology Group
SWOG: Southwest oncology group
RECIST: Response Evaluation Criteria in Solid Tumors
CVLT: California verbal learning test
CCT: Color connection test
BNRT: Benton retention test
VFT: Verbal fluency test
